### Compensation

Participants were eligible to receive up to $155 in compensation. Incentives were structured to promote sustained engagement across daily diary completion, device monitoring, and panel assessments. Participants received $1 per completed daily diary (maximum $35), with additional bonuses for achieving ≥ 50% ($15) and ≥ 80% ($15) diary completion. Incentives were also tied to Fitbit data synchronization thresholds based on valid wear days, defined as days with ≥ 1,000 recorded steps. Participants received $10 for syncing valid data on ≥ 50% of study days and another $10 for syncing ≥ 80% of study days. Participants received $10 for each completed monthly panel survey. An early engagement bonus ($10) was awarded to participants who synced valid Fitbit data on ≥ 80% of days (n = 22 days) during the first four weeks of the study. Participants received $10 for completing the second in-person assessment. Participants were permitted to keep the Fitbit device upon study completion.

### Data Analyses

#### Preparation.

Daily time-series datasets will integrate device-based 24-hour movement behaviors (sleep, SB, LPA, and MVPA), depressive symptoms, anxiety symptoms, contextual covariates, and academic load indicators. Prior to analysis, 24-hour movement behavior data will be inspected for zero values. Any observed zeros will be addressed using a log-ratio expectation–maximization (LREM) approach to permit valid compositional transformation.^97^ Daily wake-to-wake wear times will then be normalized to 1,440 minutes using the R package compositions,^98^ ensuring closure of the 24-hour composition. Movement behaviors will subsequently be transformed into isometric log-ratio (ilr) coordinates using sequential binary partitioning procedures.^99^ Four distinct sets of ilr coordinates will be constructed, each specifying a different behavior (sleep, SB, LPA, or MVPA) as the pivot coordinate (ilr ). This pivot approach enables examination of the relative importance of each behavior compared to the remaining components of the composition, while preserving the inherent co-dependence among sleep, SB, LPA, and MVPA.

#### Aim 1 (Within-Person Associations Between 24-Hour Movement Behaviors and Depressive/Anxiety Symptoms).

To examine dynamic longitudinal associations between specific depressive and anxiety symptoms and 24-hour movement behaviors, a series of multi-level vector autoregressive (mlVAR) models will be estimated.^100,101^ Each of the four time-use components that make up the 24-hour movement composition will be rotated into the ilr position to study its unique association (relative to time spent in other behaviors) in relation to each depressive and anxiety symptom. This framework allows for the simultaneous modeling of temporal (lagged), contemporaneous, and between-person associations while separating within-person dynamics from stable between-person differences.^102^ Time-lagged models will be used to examine whether day-to-day fluctuations in sleep, SB, LPA, and MVPA predict subsequent changes in specific depressive and anxiety symptoms, and vice versa. Centrality indices (strength, expected influence, betweenness, and closeness) will be computed to identify the most influential behaviors and symptoms within the network structure.

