During each 7-day burst period, participants completed a daily diary adaptation of the PHQ-8 assessing symptoms experienced since waking that day.^63^ Item selection and wording were informed by an established experience sampling repository (i.e., the ESM Item Repository) to ensure ecological validity and alignment with intensive longitudinal measurement practices.^64^ Items are presented in Supplementary Materials Table 1. The suicidality item was excluded due to safety monitoring constraints in unsupervised daily assessment contexts. To enhance conceptual specificity for network modeling, selected items were decomposed into theoretically distinct components. Specifically, the psychomotor agitation/retardation item was separated into two items distinguishing slowed movement/speech from restlessness, and the sleep item was divided to differentiate difficulty initiating or maintaining sleep (“trouble falling asleep or staying asleep”) from hypersomnia-related symptoms (“slept more than usual”). As a result of these modifications, the daily diary instrument included 10 depressive symptom items. Daily items were rated on a five-point scale ranging from 0 (“Not at all”) to 4 (“Very much”) and were administered at 8:00 pm, with automated hourly reminders at 9:00 pm and 10:00 pm before the survey closed at 11:00 pm. To support participant well-being, information about free university psychological services was provided upon completion of each daily diary.

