Beyond identifying behavior-symptom link specificity, an additional aim of this work is to determine whether shifts in behavioral time-use distributions precede periods of symptom escalation during the transition to college – a developmental window in which subthreshold symptoms may consolidate into clinically significant depressive episodes.^1,2,5^ Network theory suggests that systems may become more densely connected prior to transitions into more severe states,^113,114^ raising the possibility that time-varying symptom-behavior networks could signal emerging vulnerability. This perspective aligns with precision psychiatry initiatives such as WARN-D,^115^ which seek to detect early warning signals of depression using intensive longitudinal designs that integrate self-reports and passive sensing via wearable devices. At the same time, distinct 24-hour movement behavior composition profiles may demonstrate unique symptom-behavior network structures, suggesting that vulnerability processes differ across behavioral phenotypes. By modeling time-varying symptom-behavior networks across an academic semester, the CALM Study aims to evaluate whether changes in behavioral influence or overall network connectivity coincides with high-risk academic periods, and clarify both when and for whom behavioral perturbations are most strongly associated with symptom worsening. Although temporal associations do not establish causality, estimating lagged relationships at the daily level can generate hypotheses regarding modifiable behavioral processes that may destabilize or stabilize symptom networks during this critical developmental transition.

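### Aim 1's lagged movement-to-symptom edge adjusts for an evening diary completed after most of that day's movement, so the two lagged directions are not comparable

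*Protocol article*

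**What the plan says.** The protocol article's Data Analyses section, Aim 1, states that "a series of multi-level vector autoregressive (mlVAR) models will be estimated" and that "This framework allows for the simultaneous modeling of temporal (lagged), contemporaneous, and between-person associations". The directional question goes to the time-lagged part: "whether day-to-day fluctuations in sleep, SB, LPA, and MVPA predict subsequent changes in specific depressive and anxiety symptoms, and vice versa". Centrality indices are then computed to name the most influential behaviours and symptoms. The lag order is not written out, but the Discussion speaks of "estimating lagged relationships at the daily level", so one day is the natural reading.

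Two timing facts come from elsewhere in the article. Under Depressive Symptoms, the burst instrument is a "daily diary adaptation of the PHQ-8 assessing symptoms experienced since waking that day", and its items "were administered at 8:00 pm, with automated hourly reminders at 9:00 pm and 10:00 pm before the survey closed at 11:00 pm". Under Preparation, "Daily wake-to-wake wear times will then be normalized to 1,440 minutes". The article does not say whether a wake-to-wake window carries the date on which it starts or the date on which it ends.

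**The concern.** In an mlVAR model each node on day t is regressed on all nodes on day t-1, including its own lag. For the path from movement to a symptom, the baseline against which later change is judged is therefore the diary of day t-1. If windows carry their start date, that diary comes after most of the waking movement whose effect is being tested. Whatever movement did to mood by that evening is already in the baseline and is adjusted away. For the path from symptom to movement, the adjusting variable is the previous day's movement, most of which came before the diary, so that path is not weakened in the same way.

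At stake is the directional reading of Aim 1 and any centrality taken from the temporal network. So is the question raised in the Discussion of whether shifts in time use come before symptom escalation. If movement acts on mood mainly within the day, the lagged network will understate behaviour relative to symptoms.

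**Working it through.** **Stated design figure.** The only one is the sample size: 107 × 1.30 = 139.1, which matches the recruitment aim of 139. The 107 is simulation-based with no variance components given, so it cannot be reproduced. Nothing below rests on it.

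**Inputs from the article.** Diary at 8 to 11 pm about the time since waking; wake-to-wake movement windows; five 7-day bursts; 144 students enrolled.

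**Assumed, not in the article.** One-day lag; start-day dating unless noted; symptom autocorrelation φ = 0.3; movement autocorrelation ρ = 0.2; effects of 0.10 or 0.20 SD; diary reliability 1.0 or 0.6; 80% diary completion.

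**Order within a start-dated window.** Waking, then most SB, LPA and MVPA, then the diary, then the night's sleep.

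**Algebra.** Let S be a symptom and M daytime movement:

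- S(t) = φ·S(t-1) + β·M(t) + e
- M(t) = ρ·M(t-1) + κ·S(t-1) + u

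Substituting the second into the first gives S(t) = (φ + βκ)·S(t-1) + βρ·M(t-1) + (e + βu). The lagged movement-to-symptom edge is βρ and the lagged symptom-to-movement edge is κ. With β = -0.20 and ρ = 0.2, the first is -0.04, one fifth of the effect. With β = κ = -0.10, the edges are -0.02 and -0.10, a ratio of 1/ρ = 5.

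**Precision.** A 7-day burst gives 6 lag-1 pairs, so at most 5 × 6 = 30 per student and 144 × 30 = 4,320 in all. The standardised standard error is about 1/√4,320 = 0.015. An edge of -0.02 is then about 1.3 standard errors and one of -0.10 about 6.6.

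**Simulation.** 144 students, 400 runs per scenario, two-sided 5%. Within-person centred regressions with participant-clustered standard errors stand in for mlVAR, and movement is a single variable, not a log-ratio coordinate. Percentages are the share of runs in which the edge was detected.

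| True structure | Movement to symptom, lagged | Symptom to movement, lagged | Contemporaneous |
|---|---|---|---|
| Same-day movement effect -0.20 only | -0.041 (53%) | +0.001 (8%) | -0.196 (100%) |
| Same-day -0.10, and symptom to next-day movement -0.10 | -0.018 (17%) | -0.100 (100%) | -0.099 (100%) |
| Same pair at -0.20 | -0.036 (49%) | -0.199 (100%) | -0.197 (100%) |
| Same pair at -0.20, diary reliability 0.6 | -0.074 (82%) | -0.116 (100%) | -0.166 (100%) |
| Next-day carry-over of movement -0.10 only | -0.101 (100%) | +0.003 (6%) | 0.000 (4%) |
| No effect | +0.001 (4%) | -0.001 (5%) | 0.000 (7%) |
| Same-day -0.20 only, windows dated by end day | -0.005 (7%) | -0.179 (100%) | -0.039 (56%) |

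With equal true effects the ratios are 0.100/0.018 = 5.6 and 0.199/0.036 = 5.5. At diary reliability 0.6 the ratio falls to 0.116/0.074 = 1.6, because an error-prone diary adjusts incompletely. With ρ = 0 (and φ = 0.5), a same-day effect of -0.20 leaves a lagged edge of -0.002 (7%).

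**Time-ordered alternative.** Regressing diary t on diary t-1 and day-t movement returned -0.201 for a true -0.20 and -0.102 for a true -0.10 (same-day effect only), both detected in every run. When only next-day carry-over was present it returned -0.016 (13%), which is why the previous day's composition should also be in the model.

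**The case against.** A reader might go further and infer that the symptom-to-behaviour direction must win by construction, or that the study would report the opposite of the truth. The article does not support that. Under start-day dating, with no true reverse effect, the reverse edge stays near the nominal level (5% to 8%), and a real next-day carry-over of movement is fully recovered. The same-day association is not lost either: the planned contemporaneous network detects it, though without an arrow.

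Four further objections deserve an answer.

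- **The time-ordered model supplies direction by assumption.** This stands. In the two-variable set-up its coefficient, once the previous day's movement is included, comes from the same residual covariance as the contemporaneous edge. The good recovery above follows partly from a generating model with no within-day path from symptom to movement. Low mood in the morning that reduces afternoon activity would give the same coefficient, and a diary that looks back to waking cannot exclude it.
- **The closed composition includes sleep.** This also stands. Under start-day dating, the day-t composition contains the night after diary t, and every pivot coordinate contrasts one behaviour with the rest. The composition must be re-paired before such a model is fitted.
- **Window dating and lag order may be set in the full plan.** Their absence is therefore not counted as an error. The attenuation follows from the stated diary time under the natural reading. The other dating would be worse, since it yields a spurious reverse edge.
- **The Discussion calls lagged results non-causal and hypothesis-generating, and nowhere says the two directions will be ranked.** That limits the consequence. But Aim 1 puts both directions to the same lagged models and uses centrality to name the most influential nodes, which invites the comparison.

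**Conclusion.** The concern holds in a limited form. With a one-day lag and start-dated windows, the lagged edges from SB, LPA and MVPA to symptoms measure next-day carry-over plus about βρ of any same-day effect, while the reverse edges keep their size. Equal true effects would look unequal by about 5 to 1 at an assumed movement autocorrelation of 0.2, and by about 1.6 to 1 if diary reliability were 0.6. The two lagged directions should not be set against each other.

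With a perfectly measured diary, the direction of this imbalance needs only a same-day effect and a movement autocorrelation well below 1. Its size and the detection rates are illustrative: they depend on autocorrelations, effect sizes, diary reliability and window dating that the article does not give. The point concerns daytime movement. Under start-day dating the night's sleep follows the diary, so the path from sleep to the next day's symptoms is properly ordered. It deserves correction before analysis because it changes what Aim 1 can conclude.

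**What to change.** 1. Label lag-1 edges from SB, LPA and MVPA as next-day carry-over only. Do not use the two lagged directions, or centrality from the temporal network, as evidence of which comes first.
2. State how the wake-to-wake window is dated relative to the diary.
3. Beside the mlVAR, pre-specify one time-ordered multilevel model per rotation: diary t on a composition of the preceding night's sleep plus day-t waking SB, LPA and MVPA, adjusting for diary t-1 and the previous day's composition. This pairing keeps sleep after the diary out of the exposure.
4. Report it beside the symptom(t-1)-to-behaviour(t) result as an ordered association, not as proof of direction.

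The cost is a few extra models and some wording; no new data are needed. The time order remains partial, because the diary looks back to waking and some movement occurs after 8 pm.

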#### Aim 3 (Periods of Heightened Risk for Symptom Onset and Progression).

To examine the temporal stability of the depression symptom network across the first college term, including 24-hour movement behaviors and anxiety symptoms as nodes, time-varying network analyses will be conducted using rolling 7-day calendar windows across the 108-day study period.^103^ Although participants contributed data during assigned burst weeks only, pooled daily observations across individuals provide coverage spanning the full academic term. Within each window, mlVAR models will be estimated to derive temporal (lagged) and contemporaneous networks while accommodating the unbalanced repeated-measures structure of the burst design. Window-specific network metrics, including global connectivity (e.g., average edge weight), network density, and node centrality indices, will be computed to evaluate changes in overall interconnectedness and node influence over time. Periods characterized by increased network connectivity or heightened centrality of specific symptoms or behaviors will be interpreted as potential windows of increased vulnerability – or, conversely, relative stability – during the transition to college. Calendar-based academic or institutional events (e.g., midterm periods, finals week, university-designated mental health initiatives such as Wildcat Pause Day) will be descriptively overlaid onto temporal network estimates to contextualize observed patterns.

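### Aim 1 centrality, if summed over all edges of networks with ilr-coded behaviour nodes, depends on the coordinate coding, so a symptom or behaviour has no unique strength or expected influence

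*Protocol article*

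**What the plan says.** The protocol article, Data Analyses, Preparation, fixes the coding of the behaviours: "Movement behaviors will subsequently be transformed into isometric log-ratio (ilr) coordinates using sequential binary partitioning procedures". It continues: "Four distinct sets of ilr coordinates will be constructed, each specifying a different behavior (sleep, SB, LPA, or MVPA) as the pivot coordinate". The stated reason is that "This pivot approach enables examination of the relative importance of each behavior compared to the remaining components of the composition".

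Aim 1 then says that "a series of multi-level vector autoregressive (mlVAR) models will be estimated" and that "Each of the four time-use components that make up the 24-hour movement composition will be rotated into the ilr position", so several networks are fitted to the same data. The same section ends: "Centrality indices (strength, expected influence, betweenness, and closeness) will be computed to identify the most influential behaviors and symptoms within the network structure". It refers to one network structure and does not say which of the four networks supplies a symptom's value.

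Aim 3 describes the network as "including 24-hour movement behaviors and anxiety symptoms as nodes" and computes node centrality again in each rolling window, without naming the indices. It reads raised centrality of a symptom or behaviour as a possible window of vulnerability.

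**The concern.** Four behaviours give three ilr coordinates per set. Only the pivot stands for a named behaviour (that behaviour relative to the other three). The remaining two are balances whose order and sign carry no meaning of their own and are not stated.

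Strength adds absolute edge weights and expected influence adds signed ones. Neither sum is preserved when one set of ilr coordinates is exchanged for another. If edges to all three coordinates are counted, the same data and the same fit give each symptom up to four values, and the plan names no rule for choosing among them. A behaviour's own index has a similar problem, because it includes edges to the two balances. What is at stake is the naming of the most influential symptoms and behaviours in Aim 1, and any reading of centrality over time in Aim 3.

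**Working it through.** The plan gives no centrality figure to reproduce, so the check is algebra, a worked example and a simulation.

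**Inputs from the article.** Four behaviours, hence three coordinates per set, and four sets (Preparation). Symptom nodes: "the daily diary instrument included 10 depressive symptom items", plus 6 daily anxiety items (Measures), so 10 + 6 = 16 symptoms and up to 16 + 3 = 19 nodes.

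**Assumed, not in the documents.** All three coordinates are nodes; the coefficients used below.

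**Step 1, algebra.** Let b be a symptom's coefficients on the four log-parts (summing to zero) and V the 4 x 3 orthonormal basis of a rotation. The ilr coefficients are g = V'b. Two bases differ by an orthogonal matrix, so the sum of g² is constant, while the sum of |g| (strength) and the sum of g (expected influence) are not. For three coordinates the sum of |g| lies between 1 and √3 = 1.73 times the root sum of squares.

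**Step 2, example.** Only sleep versus the rest acts on the symptom: b = (-0.12, 0.04, 0.04, 0.04) for sleep, SB, LPA, MVPA. With parts ordered 1 to 4:

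- g1 = √(4/3) × b1
- g2 = √(2/3) × (b2 - (b3 + b4)/2)
- g3 = √(1/2) × (b3 - b4)

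| Order (pivot first) | g1 | g2 | g3 | Sum of absolute values | Signed sum |
|---|---|---|---|---|---|
| sleep, SB, LPA, MVPA | -0.1386 | 0 | 0 | 0.139 | -0.139 |
| SB, LPA, MVPA, sleep | 0.0462 | 0.0653 | 0.1131 | 0.225 | +0.225 |
| LPA, MVPA, sleep, SB | 0.0462 | 0.0653 | -0.1131 | 0.225 | -0.002 |
| MVPA, sleep, SB, LPA | 0.0462 | -0.1306 | 0 | 0.177 | -0.084 |

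The sum of squares is 0.0144 + 3 × 0.0016 = 0.0192 in every row.

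**Step 3, same pivot, other parts reordered.** With SB as pivot, the order SB, sleep, LPA, MVPA gives (0.0462, -0.1306, 0), with signed sum -0.084. The order SB, LPA, MVPA, sleep gives +0.225. The pivot coefficient stays at 0.0462. Fixing the pivot therefore does not fix the index.

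**Step 4, share of a symptom's total.** The movement in strength is 0.225 - 0.139 = 0.086. If the 15 other symptoms contribute mean absolute edges of 0.02 to 0.10 (assumed), they add 0.30 to 1.50. The change in total in-strength is then 0.086/0.439 = 20% down to 0.086/1.639 = 5%.

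**Step 5, effect on rankings.** 300 population VAR(1) systems per setting were simulated with 16 symptoms and 3 ilr nodes, standardised edges and no sampling error. The SD of the lagged symptom-behaviour coefficients was 0.03 to 0.08, and MVPA had the largest log-ratio variance (both assumed).

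| Symptom index | Top symptom differs between pivots | Mean lowest rank correlation between pivots |
|---|---|---|
| Lagged out-strength | 23% to 62% | 0.95 to 0.86 |
| Lagged out-expected influence | 55% to 88% | 0.77 to 0.25 |
| Contemporaneous strength | 31% | 0.95 |
| Contemporaneous expected influence | 55% | 0.77 |

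Reordering only the non-pivot parts moved the pivot node's own out-strength by 0.05 on average (up to 0.14) and its expected influence by 0.26 (up to 0.60).

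**Step 6, what does not move.** With all three coordinates in the model, symptom-symptom edges were identical across the four pivots, and pivot-symptom edges were identical under reordering of the other parts, to about 6 × 10⁻¹⁶.

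**Step 7, the other reading.** If only the pivot is a node and the other two coordinates are left out of the model, each model conditions on a different variable. Symptom-symptom edges can then differ between the four models, and symptom centrality is again not unique.

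**The case against.** The strongest reply is that the article is condensed. It nowhere says that all three coordinates are nodes or that every edge counts; the two non-pivot coordinates could be adjustment terms, and scoring rules may sit in a fuller plan. It is right that the node set is inferred, from Preparation, Aim 1 and Aim 3 together. But the article does commit to the coding, the rotations, the indices and the inference drawn from them. Run as written on all nodes, these give coding-dependent values, and leaving the other coordinates out of the model does not cure that.

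A reader might infer more than the documents support:

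- **That the rotation is arbitrary.** The four pivots are pre-specified and each has a stated meaning. Only the order and sign of the remaining coordinates are arbitrary.
- **That centrality cannot identify influential nodes at all.** Symptom-symptom and pivot-symptom edges are invariant, so indices restricted to them are usable. Strength rankings often agreed closely across pivots.
- **That the plan ranks four mutually dependent pivots inside one network.** It plans a series of models. The four unstandardised pivot coefficients do sum to zero (-0.1386 + 3 × 0.0462 = 0), but Aim 1 already treats each effect as relative to the other behaviours.
- **That strength may be wrong by a factor of 1.73.** That bounds only the behaviours' share; Step 4 shows a much smaller effect on the total.
- **That the primary result is at risk.** The sample size section puts the primary hypotheses on within-person daily associations, and the abstract describes the primary analysis the same way, without centrality.

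Dropping betweenness and closeness altogether would be partly a matter of preference; no figure here shows how far they move.

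**Conclusion.** The concern holds for centrality summed over all edges. With three ilr coordinates as nodes, strength and above all expected influence are not invariant to the pivot or to the order and sign of the other coordinates. The same fit can give a symptom up to four values and change which symptom ranks first. The non-invariance is algebra and depends on no sample size; the simulated percentages depend on the assumed coefficients.

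The edge-level behaviour-symptom associations are not affected when all three coordinates are in the model. That invariance is exact for a VAR with common fixed effects. Random effects restricted to be uncorrelated, or regularised edges, could break it.

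**What to change.** Amend the Aim 1 wording as follows:

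- Keep all three ilr coordinates in every model.
- Compute symptom centrality over symptom-symptom edges only.
- Report each behaviour's strength and expected influence from its pivot-to-symptom edges, in the rotation where it is the pivot, interpreted as relative to the other behaviours.
- Exclude edges to and among non-pivot coordinates from all centrality indices, including any path-based ones that are kept.
- Apply the same rule to the node centrality indices in Aim 3.

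Optionally, give total behavioural influence on a symptom as the root sum of squares over the three unstandardised coordinates. This is the same in every rotation (√0.0192 = 0.139 in the example).

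The cost is analysis wording; no new data are needed. The downside is that fewer or narrower indices are reported, and symptom centrality no longer includes links to behaviour.
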